#### Data collection

All data will be recorded daily in the dedicated case report form for the entire duration of the study. The following data will be recorded:for each patient: Simplified Acute Physiology Score II, Sequential Organ Failure Assessment score at randomization, demographic data (age, sex, weight, height, comorbidities, clinical and microbiological data to confirm the diagnosis of catheter-related infection (if any)), monitoring (type of RRT, continuous or intermittent RRT, duration of each RRT session and use of systemic anticoagulant) and general complications (bleeding, thrombosis or systemic infection).for each catheter: insertion date, insertion site, catheter removal date, reason for catheter withdrawal, use of ultrasound guidance, experience of the operator (junior, (resident in training), senior with under two years’ experience or senior with more than two years’ experience), need for antibiotic therapy due to suspected or confirmed catheter infection, puncture site bleeding, hematoma, thrombosis, local signs of infection and microbiology (catheter culture, puncture site culture and blood culture).

#### Study definitions

##### Dysfunction

Catheter dysfunction is defined as the inability to achieve and maintain a blood flow of more than 200 mL/min despite changing the patient’s position, inverting the lines and flushing with saline solution. The occurrence of any one or more of these events (such as a change of position, inversion of a line or flush of saline solution) will be considered as catheter dysfunction.

Catheter thrombosis will be treated by the injection of 5,000 to 10,000 IU/mL of urokinase in each lumen of the catheter with a volume equivalent to that of the catheter (noted on each catheter). After 15 minutes, the urokinase will be aspirated with a syringe and dialysis will resume. If urokinase treatment fails to resolve catheter thrombosis, the catheter will be changed [39, 40].

Cather-related infections include the following:Local catheter-related infection, defined as a positive catheter-tip culture of 10^3^ CFU/ml or more, with the presence of pus or oozing at the catheter insertion site, or tunnelitis.General catheter-related infection, defined as a positive catheter-tip culture of 10^3^ CFU/ml or more, with the disappearance of general signs of infection within 48 hours after catheter withdrawal.Catheter-related blood stream infection, defined as the presence of fever (temperature > 38°C) and a positive blood culture taken from the dialysis catheter and a peripheral line in the absence of any other source of infection, with a central-to-peripheral quantitative blood culture ratio of over five, or a differential period of central line culture versus peripheral blood culture positivity for more than two hours, with a central hemoculture showing a positive result more quickly than a peripheral culture.

Systematic samples will be performed at the puncture site in case of any change in skin colour (for example, redness) and/or the presence of pus or oozing suggestive of infection. All samples will be analyzed by the bacteriology laboratory. If infection is confirmed, antibiotic therapy will be initiated. A clinical event committee comprising two physicians ([name], from the Department of Epidemiology and Hospital Hygiene, University Hospital of Dijon, and [name], from the Department of Infectiology, University Hospital of Dijon, France) blinded to the treatment allocation will independently analyze data and adjudicate as to the presence or not of catheter infection. Bleeding complications are defined as a drop in hemoglobin levels requiring the transfusion of at least two units of packed red blood cells.

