To the best of our knowledge, only one randomized study, which included 291 patients, has compared the safety and efficacy of heparin versus citrate as a locking solution for non-tunneled catheters in hemodialysis patients [15]. The risk of catheter dysfunction was significantly lower in the citrate group, at 5 versus 8.1 events per 1,000 catheter days for citrate versus heparin respectively (relative risk (RR) 0.38, *P* = 0.015). The authors also noted a lower incidence of catheter infection in the citrate group (1.4 out of 1,000 catheter days) as compared to the heparin group (3.9 out of 1,000 catheter days) (RR 0.36, 95%CI 0.13 to 1.00, *P* = 0.05). Furthermore, the risk of bleeding and death from catheter-related bacteremia was significantly lower in the citrate group. Indeed, it should be noted that this study was prematurely interrupted because of a significant difference in catheter-related bacteremia between groups, in favor of the citrate group. Nevertheless, in this same study, the citrate concentration used was 30% (instead of 4%), and patients in intensive or critical care were excluded.

The primary objective of our study is to demonstrate the superiority of trisodium citrate 4% over heparin as a catheter lock solution, in terms of event-free survival of the first non-tunneled hemodialysis catheter inserted in patients hospitalized in intensive or critical care for AKI requiring extracorporeal RRT. Secondary objectives are to compare the rate of fibrinolysis, incidence of catheter thrombosis and catheter-related infection per 1,000 catheter days, length of stay in an ICU, and in-hospital and 28-day mortality.

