#### Study treatments

Citrate or heparin, according to the study group, will be instilled into each lumen of the catheter to attain a total volume corresponding to the volume of each branch according to the Summary of Product Characteristics. Before each administration of citrate or heparin, the catheter lumens will be flushed with 10 mL of saline as quickly as possible. Then, the lock solution (heparin or citrate) will be injected slowly (over at least 10 seconds duration) into each lumen.

Before initiation of RRT and use of the catheter, a minimum of 5 cc of liquid will be extracted from each lumen (volume greater than the contents of each lumen). Catheter patency will be verified by performing a blood return with a 20 cc syringe. If the 20 cc syringe fills smoothly in under four seconds, this corresponds to a blood flow of 300 mL/min on the hemodialysis machine. All catheters used will have a minimum diameter of 13.5 French. Only one catheter per patient will be considered for the study analysis.

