#### Secondary endpoints

Secondary endpoints are: the rate of fibrinolysis per 1,000 catheter days, the incidence of catheter dysfunction per 1,000 catheter days, the incidence of catheter-related infection per 1,000 catheter days, the number of hemorrhagic events requiring the transfusion of at least two units of packed red blood cells, length of stay in intensive or critical care, length of hospital stay and in-hospital and 28-day mortality rate.

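### Catheter dysfunction is defined in two incompatible ways, so the secondary endpoint that counts it is ambiguous

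*Protocol article*

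**What the plan says.** Under Study definitions, the first sentence on dysfunction reads: "Catheter dysfunction is defined as the inability to achieve and maintain a blood flow of more than 200 mL/min despite changing the patient’s position". It then adds the other two measures that must also have been tried ("position, inverting the lines and flushing with saline solution"). The next sentence makes any one of those measures sufficient: "change of position, inversion of a line or flush of saline solution) will be considered as catheter dysfunction". It contains no flow threshold and no condition that the measure failed.

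The definition feeds a listed secondary endpoint, "the incidence of catheter dysfunction per 1,000 catheter days". The Abstract and the Background word the matching secondary objective differently: "incidence of catheter thrombosis and catheter-related infection per 1,000 catheter days". Thrombosis is given a treatment under Study definitions but no diagnostic criterion.

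A saline flush is also part of routine care in both arms. Study treatments states: "Before each administration of citrate or heparin, the catheter lumens will be flushed with 10 mL of saline as quickly as possible". Patient management lists a catheter flush among the steps that close each session.

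The Discussion describes dysfunction only as a failure to reach and hold a flow adequate for the dialysis dose.

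**The concern.** The two sentences classify the same episode differently. Poor flow that recovers after one repositioning is not dysfunction under the first sentence and is dysfunction under the second. The second cannot be read as a gloss on the first. Any episode that satisfies the first has already involved the manoeuvres, so it satisfies the second as well, and the flow threshold then does no work.

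At stake is what the reported rate means. Six units in two hospitals record these events. The clinical event committee, as described, rules on infection only, so no described step would bring divergent use of the two rules back to one. If the rule is settled after unblinding, the choice is open to the charge that it followed the data. The switch between thrombosis and dysfunction adds a smaller uncertainty about which quantity the secondary objective concerns.

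**Working it through.** There is no planned figure to reproduce: the document sets no target, power or expected rate for dysfunction. The check is a comparison of the text, followed by what can and cannot be said about size.

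**Step 1. Apply both sentences to the same situations.**

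| Situation | First sentence | Second sentence |
|---|---|---|
| Low flow persists after all three manoeuvres | event | event |
| Low flow corrected by one manoeuvre | not an event | event |
| Routine flush before a lock, flow adequate | not an event | in context not an event, but not expressly excluded |

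The second row is the contradiction. The third is a gap in the wording.

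**Step 2. Direction of the difference in the rate.** In one arm, let F be the number of low-flow episodes that persist, M the number corrected by a manoeuvre, and T the catheter days, with each episode counted once.

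- First sentence: rate = 1,000 × F / T
- Second sentence: rate = 1,000 × (F + M) / T

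Because M cannot be negative, the second rate is never lower than the first. The gap is 1,000 × M / T. The document gives no value for M, so the gap cannot be computed.

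**Step 3. Direction of the difference in the rate ratio.** Let w be the share of F in (F + M) in the heparin arm, RR_F the citrate-to-heparin rate ratio for persistent failures, and RR_M that for corrected episodes. Then

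ratio under the second sentence = w × RR_F + (1 − w) × RR_M

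If RR_M = 1, the ratio is pulled towards 1. If RR_M = RR_F, it does not change and there are simply more events. The document gives neither w nor RR_M, so the sign and size of any distortion are open.

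**Step 4. Scale of the extreme reading in which every pre-lock flush counts.** The number of locks per catheter day is not given; I assume 0.5 to 1. For scale, the Background cites dysfunction rates of 5 (citrate) and 8.1 (heparin) per 1,000 catheter days from an earlier trial. It prints a relative risk of 0.38 beside them, although 5 / 8.1 = 0.617, so they serve as an order of magnitude only.

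- Routine flushes: 1,000 × 0.5 = 500 to 1,000 × 1 = 1,000 per 1,000 catheter days in each arm
- Ratio with 500 added: (5 + 500) / (8.1 + 500) = 505 / 508.1 = 0.994
- Ratio with 1,000 added: (5 + 1,000) / (8.1 + 1,000) = 1,005 / 1,008.1 = 0.997

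Under that reading the endpoint would be little more than a count of lockings. This is a reason to think the reading is not intended; it does not estimate what sites will record.

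**The case against.** A reader might infer that every locking counts as a dysfunction and that the endpoint is therefore unusable. The document does not support this. The second sentence points back to the manoeuvres just listed, which are attempts to rescue poor flow. The routine flush comes before a lock, after the dialysis lines have been removed, and no section calls it an event. What remains is that the wording does not exclude it.

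A reader might also infer that the looser rule must bias the comparison towards no effect. That would follow if the extra events had nothing to do with the lock. Repositioning, inversion or flushing done because flow is poor may well reflect how the lock performed, and Step 3 shows that the result can then go either way.

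Three further points limit the concern:

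- The primary endpoint is time to catheter withdrawal. The sample size and the interim test rest on that endpoint. The Discussion does word the working hypothesis in terms of dysfunction, but the Background states the primary objective as event-free catheter survival.
- Those who manage the patients are meant to be blinded, so there is no evident reason for the choice of rule to differ by arm. The problem is one of meaning and consistency more than of a tilted comparison.
- The Discussion concedes that definitions of dysfunction vary and cites frequencies of 10.7% and 31.5%. Comparison with earlier work is limited under either rule.

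All three stand, and they lower the severity. None says which sentence governs.

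**Conclusion.** The contradiction is real and can be seen on the page: an episode corrected by a single manoeuvre is an event under one sentence and not under the next. The secondary endpoint is ambiguous as written, but it is repairable. Its rate is at least as high under the second rule as under the first, assuming each episode is counted once. Neither the size of that difference nor its effect on the treatment comparison can be derived from the document. This is a should-fix internal inconsistency in a secondary endpoint, and it leaves the primary analysis untouched.

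**What to change.** Before any unblinded look at the data:

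1. Reconcile the two sentences into one definition that governs the endpoint. The choice is the sponsor's; the flow-failure sentence is the one consistent with the Discussion.
2. Record manoeuvres that restore flow as a separate descriptive variable, so that this information is kept.
3. State that the routine saline flush before a lock or at the end of a session is not an event.
4. Use one term, dysfunction or thrombosis, in the Abstract, the Background objectives and the list of secondary endpoints. If thrombosis is kept as an outcome, give it a criterion.
5. Apply the chosen rule, blinded to allocation, to patients already enrolled where the recorded data allow, and report how many could not be classified.

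Items 1 to 4 cost a short amendment and a note to sites. The cost of item 5 is unknown: the Data collection list names neither the flow achieved nor the manoeuvres used, and the full case report form is not shown. Timing matters, since 191 patients had been recruited at submission and the interim analysis is planned at 200.

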### Study endpoints

#### Primary endpoint

The primary endpoint is the duration of event-free survival of the first non-tunneled dialysis catheter, defined in days as the time from randomization to catheter withdrawal, whatever the reason (infection, thrombosis, leakage or deteriorated catheter and unintentional or accidental catheter removal).

#### Secondary endpoints

Secondary endpoints are: the rate of fibrinolysis per 1,000 catheter days, the incidence of catheter dysfunction per 1,000 catheter days, the incidence of catheter-related infection per 1,000 catheter days, the number of hemorrhagic events requiring the transfusion of at least two units of packed red blood cells, length of stay in intensive or critical care, length of hospital stay and in-hospital and 28-day mortality rate.

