## Abstract

**Background:**

The incidence of acute kidney injury (AKI) is estimated at 10 to 20% in patients admitted to intensive care units (ICU) and often requires renal replacement therapy (RRT). ICU mortality in AKI patients can exceed 50%. Venous catheters are the preferred vascular access method for AKI patients requiring RRT, but carry a risk of catheter thrombosis or infection. Catheter lock solutions are commonly used to prevent such complications. Heparin and citrate locks are both widely used for tunneled, long-term catheters, but few studies have compared citrate versus heparin for patients with short-term, non-tunneled catheters. We aim to compare citrate 4% catheter lock solution versus heparin in terms of event-free survival of the first non-tunneled hemodialysis catheter inserted in ICU patients with AKI requiring RRT. Secondary objectives are the rate of fibrinolysis, incidence of catheter thrombosis and catheter-related infection per 1,000 catheter days, length of stay in ICU and in-hospital and 28-day mortality.

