#### Patient management

Daily monitoring of all patients will be performed in accordance with standard practices for patients undergoing RRT. Hemodialysis catheters will be used for the purpose of RRT only (no infusions will be administered through the catheters). For hemodialysis catheter management, two nurses will be present. One will work in aseptic conditions (as for an operating theatre) to manage RRT initiation (withdrawal of lock solution, patency check by blood return and connection of the dialysis lines to the catheter) and completion (remove dialysis lines, flush catheter, insert catheter lock solution and bandage). The second nurse will oversee the control panel and working of the dialysis machine. Hemodynamic monitoring of the patient is performed continuously during RRT, including monitoring of dialysis circuit pressures and transmembrane pressure.

Signs of thrombosis are recorded every time the catheter is connected to the dialysis machine. Signs of infection are recorded several times daily, with measurement of the patient’s temperature every three hours and daily surveillance of the puncture site. Samples will be obtained by swabbing the skin in case of suspected infection, in addition to blood samples. In case of suspected or confirmed infection, the catheter will systematically be removed and the need for antibiotic therapy will be discussed by the medical team. If and when identified, the germs responsible for the infection will be noted. Bleeding complications will also be recorded, defined as a drop in hemoglobin levels requiring transfusion of at least two packs of red blood cells, in cases of major bleeding, and number of packs of red blood cells transfused.

Insofar as possible, the catheter will be removed before patient discharge. Patients will be followed up for the duration of their hospital stay.

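### The secondary objective of catheter thrombosis incidence has no matching endpoint: the endpoint list has cause-blind catheter dysfunction in its place

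*Protocol article*

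**What the plan says.** **Objectives.** The abstract reads: "Secondary objectives are the rate of fibrinolysis, incidence of catheter thrombosis and catheter-related infection per 1,000 catheter days". The last paragraph of the Background says the same: "Secondary objectives are to compare the rate of fibrinolysis, incidence of catheter thrombosis and catheter-related infection per 1,000 catheter days". Both places treat fibrinolysis, thrombosis and infection as three separate items.

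**Endpoints.** Between fibrinolysis and infection, the Secondary endpoints section lists "the incidence of catheter dysfunction per 1,000 catheter days". Bleeding, lengths of stay and mortality come after these three. It has no thrombosis endpoint.

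**Definitions.** Under Study definitions: "Catheter dysfunction is defined as the inability to achieve and maintain a blood flow of more than 200 mL/min despite changing the patient’s position", with line inversion and saline flushing as further manoeuvres that must have failed. The next sentence says that the occurrence of any one of those manoeuvres is itself to be considered dysfunction. The section then turns to management: "Catheter thrombosis will be treated by the injection of" urokinase. It does not say which dysfunctions are thrombosis.

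**Recording.** Patient management states: "Signs of thrombosis are recorded every time the catheter is connected to the dialysis machine". Data collection lists thrombosis and the reason for withdrawal among the items recorded for each catheter. The Primary endpoint section names thrombosis as one reason for withdrawal.

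**The concern.** An objective and the endpoint that is meant to answer it should concern the same event. Here the objective is about clotting, while the listed endpoint is about flow or about handling of the catheter, whatever the cause.

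The difference matters because both study solutions are anticoagulant locks, and the Background explains their action through coagulation. A lock can plausibly affect clot in the lumen; a malpositioned or kinked catheter is a different problem. If dysfunction is reported as the answer to the thrombosis objective, flow problems common to both arms are counted with clotting events. A difference in clotting could then be blurred, or a difference in dysfunction could be described as a difference in thrombosis.

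**Working it through.** The plan gives no figure for this point, so there is none to reproduce. The check is a comparison of sections.

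**Step 1: objectives against endpoints.**

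| Objective (abstract and Background) | Secondary endpoints section |
|---|---|
| Rate of fibrinolysis | Rate of fibrinolysis |
| Incidence of catheter thrombosis | Incidence of catheter dysfunction |
| Incidence of catheter-related infection | Incidence of catheter-related infection |

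Two of the three rows agree and the middle one does not. The thrombosis objective appears in two places.

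**Step 2: are the two terms interchangeable?** The definition has to be read sentence by sentence.

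- First sentence: flow that cannot be brought and kept above 200 mL/min despite the manoeuvres. A problem solved by repositioning does not count. A persistent mechanical problem does, as does a clot.
- Second sentence: any one manoeuvre counts. A problem solved by moving the patient now counts.

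The sentences conflict over problems that respond to a manoeuvre. Under either, events without thrombosis are included, so the terms are not interchangeable. The Background's gloss of dysfunction as stenosis and/or thrombosis also makes thrombosis only one component.

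**Step 3: does another endpoint fill the gap?**

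- Fibrinolysis rate: same unit (per 1,000 catheter days), and urokinase is prescribed for thrombosis. It counts treated episodes only and is listed as its own objective, so it is a partial proxy.
- Primary endpoint: thrombosis is one withdrawal reason within a composite time to event, not an incidence per 1,000 catheter days.

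Neither is the missing endpoint.

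**Step 4: can a thrombosis endpoint be derived?** The article says that three items are recorded: thrombosis per catheter, signs of thrombosis at each connection, and reason for withdrawal. It does not list failure to aspirate a lumen, or urokinase use, as recorded items, so a definition should not rest on those without checking the case report form.

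**Step 5: direction of any dilution.** Let *p* be the share of control-arm dysfunctions that are not thrombotic, assume their rate is equal in the two arms, and let *R* be the rate ratio for thrombotic events. The ratio seen on dysfunction is then

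*p* × 1 + (1 − *p*) × *R*,

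which lies nearer to 1 than *R* whenever *p* > 0. Purely as an assumed illustration with *R* = 0.60: *p* = 0.25 gives 0.25 + 0.75 × 0.60 = 0.70, and *p* = 0.50 gives 0.50 + 0.50 × 0.60 = 0.80. The documents supply neither *p* nor *R*. The formula shows the direction under its assumption; the values say nothing about this trial.

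**The case against.** The strongest reply is that dysfunction is what the authors mean throughout. The earlier citrate trial is summarised by its dysfunction rates, and the Discussion states both its evidence aim and its working hypothesis in terms of dysfunction. The slip may then lie in the objectives, where changing one word would repair it. This is a fair reading, and the fix allows for it. It does not remove the contradiction, since objectives and endpoints would still have to be aligned.

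A second reply is that fibrinolysis already measures clotting. This stands in part. A reader might infer that the trial leaves clotting unmeasured, and the documents do not support that: treated thrombosis is captured by the fibrinolysis rate, and withdrawal for thrombosis counts in the primary endpoint. But the objectives list fibrinolysis and thrombosis separately.

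A third reply is that this is a condensed article, and that criteria for thrombosis may sit in the full protocol or the case report form guide. That also stands. The absence of a diagnostic criterion is not in itself the finding. What remains is that two lists printed in the same article disagree.

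Finally, a reader might take the dysfunction frequencies of 10.7% and 31.5% in the Discussion as proof that the outcome swings with its definition. They come from two different cited studies, and the Discussion attributes variation to catheter, lock, patient, therapy and maintenance factors. They do not isolate the definition.

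**Conclusion.** The point holds as a mismatch between a stated secondary objective and the endpoint list. The thrombosis objective has no matching endpoint, and the item in its place includes non-thrombotic events under either sentence of its definition. Fibrinolysis covers part of the question.

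The consequence is limited to secondary endpoints. The primary endpoint, sample size, significance level and interim analysis are unaffected. Whether dysfunction would understate an effect on clotting, and by how much, cannot be estimated: that depends on the split between thrombotic and other dysfunctions and on their rates by arm, none of which the documents give. The conclusion rests on the text alone and assumes only that the objective means what it says. It is worth correcting because the remedy is cheap and lets the trial answer its own question.

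**What to change.** Before unblinding:

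1. Add catheter thrombosis per 1,000 catheter days to the secondary endpoints. Derive it by a stated rule from the items the article says are recorded: thrombosis per catheter, signs of thrombosis at connection, and withdrawal for thrombosis. First confirm that the per-catheter thrombosis item means clot in the catheter; it is listed beside local complications such as hematoma.
2. Avoid circularity. Fibrinolysis should not both define thrombosis and then be classified by that definition.
3. Keep dysfunction as a separate endpoint, and reconcile the two sentences of its definition so that it is clear whether a problem resolved by a manoeuvre counts.
4. Alternatively, if the sponsor means dysfunction, restate the objective as dysfunction in the abstract and the Background, and draw no conclusion about thrombosis from it.

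The cost is wording plus one more secondary endpoint, likely with fewer events and so a less precise estimate. The three core items are already collected. The alternative in item 4 adds no endpoint but gives up the question specific to clotting, except as far as fibrinolysis answers it.
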